## Abstract

**Background:**

Despite progresses in neonatal care, the mortality and the incidence of neuro-motor disability after perinatal asphyxia have failed to show substantial improvements. In countries with a high level of perinatal care, the incidence of asphyxia responsible for moderate or severe encephalopathy is still 2–3 per 1000 term newborns. Recent trials have demonstrated that moderate hypothermia, started within 6 hours after birth and protracted for 72 hours, can significantly improve survival and reduce neurologic impairment in neonates with hypoxic-ischemic encephalopathy. It is not currently known whether neuroprotective drugs can further improve the beneficial effects of hypothermia. Topiramate has been proven to reduce brain injury in animal models of neonatal hypoxic ischemic encephalopathy. However, the association of mild hypothermia and topiramate treatment has never been studied in human newborns. The objective of this research project is to evaluate, through a multicenter randomized controlled trial, whether the efficacy of moderate hypothermia can be increased by concomitant topiramate treatment.

**Methods/Design:**

Term newborns (gestational age ≥ 36 weeks and birth weight ≥ 1800 g) with precocious metabolic, clinical and electroencephalographic (EEG) signs of hypoxic-ischemic encephalopathy will be randomized, according to their EEG pattern, to receive topiramate added to standard treatment with moderate hypothermia or standard treatment alone. Topiramate will be administered at 10 mg/kg once a day for the first 3 days of life. Topiramate concentrations will be measured on serial dried blood spots. 64 participants will be recruited in the study. To evaluate the safety of topiramate administration, cardiac and respiratory parameters will be continuously monitored. Blood samplings will be performed to check renal, liver and metabolic balance. To evaluate the efficacy of topiramate, the neurologic outcome of enrolled newborns will be evaluated by serial neurologic and neuroradiologic examinations. Visual function will be evaluated by means of behavioural standardized tests.

**Discussion:**

This pilot study will explore the possible therapeutic role of topiramate in combination with moderate hypothermia. Any favourable results of this research might open new perspectives about the reduction of cerebral damage in asphyxiated newborns.

**Trial registration:**

Current Controlled Trials ISRCTN62175998; ClinicalTrials.gov Identifier NCT01241019; EudraCT Number 2010-018627-25

## Background

### Neonatal hypoxic-ischemic encephalopathy: disease incidence and pathogenesis

In countries with a high level of perinatal care, the incidence of asphyxia responsible for moderate or severe encephalopathy is 2–3 per 1000 term infants
[1,2]. The ensuing encephalopathy may present with need for resuscitation at birth, neurological depression, seizures or electroencephalographic (EEG) abnormalities. Hypoxic ischemic encephalopathy (HIE) is still the leading cause of perinatal mortality and severe neurological impairment. Mortality rate is 10% for moderate and 60% for severe HIE. About 30% of survivors with moderate and 100% with severe HIE exhibit permanent neurological disability
[3,4].

Encephalopathy results from the combination of reduced cerebral oxygenation (hypoxemia) and/or reduced perfusion (ischemia). Cerebral damage develops in two distinct phases. During the acute phase neuronal death occurs by necrosis of neuronal cells, a result of a rapid depletion of brain energy. However, after a few hours, cerebral energy metabolism recovers, but a cascading series of biochemical events triggers neuronal apoptosis and leads to severe brain damage. These events include an increased release of excitatory neurotransmitters, especially glutamate
[5]. Glutamate acts on three classes of receptors that control the passage of ion channels through the neural cell membrane: alpha-amino-3-hydroxy-5-methyl-4-isoxazolepropionate (AMPA), kainate and *N*-methyl-D-aspartate (NMDA) receptors. Neurons (and glia) contain high concentrations of glutamate, which is usually released in small amounts and for short periods of time (milliseconds)
[6]. Exceedingly high glutamate concentrations can over-excite nervous cells and lead to their death (excito-toxicity)
[7]. This excito-toxicity contributes to neuronal damage in various neurodegenerative disorders.

Glutamate activates AMPA receptors, depolarizes the cell and promotes the removal of the voltage-dependent block operated by Mg^++^[8,9] on NMDA receptors: this promotes the entry of Ca^++^ through this channel
[10]. Calcium entry stimulates in turn a series of processes that lead to necrosis and apoptosis. These processes include the Ca^++^ overload in the mitochondria, responsible for the production of free radicals
[6,11-13]; the activation of caspases and the release of factors inducing apoptosis
[14-17]; the activation of a neuronal nitric oxide synthase (nNOS) that triggers the synthesis of nitric oxide (NO) and the formation of toxic peroxynitrite and nitrosylated-GAPDH; the stimulation of p38 mitogen-activated protein kinase (p38 MAPK), which activates the transcription of factors that enter the nucleus and promote neuronal damage and apoptosis
[18-22].

Between the acute initial damage and the ensuing damage mediated by the release of toxic substances, there is therefore a time window that could offer the possibility of a combined neuroprotective treatment.

### Hypothermia as a neuroprotective treatment in animals

Currently the most effective neuroprotective intervention for asphyxiated infants is treatment with moderate hypothermia, a reduction in body temperature of 3-4°C. Experimental studies performed in adult and newborn animals have shown that reducing brain temperature by 2-4°C after ischemia protects the brain from neuronal damage and cell death and improves neurological
[23-26] and behavioral outcome, as well as histological changes
[27-29]. Several mechanisms may explain these benefits: hypothermia reduces the accumulation of extracellular glutamate, enhancing post-ischemic glutamate re-uptake
[30], the synthesis of free radicals and nitric oxide
[15], preserves the content of high-caloric cerebral phosphates, reduces cerebral alkalosis and lactate levels
[16,31]. Hypothermia may also suppress the activation of microglia
[32-34]. These actions can preserve brain energy metabolism, reduce cytotoxic cerebral edema and inhibit neuronal death. Thanks to animal experiments, the optimal temperature for brain neuroprotection, leading to reduce biochemical and histological markers of neuronal damage, has been observed to be between 32 and 34°C
[13,35-37]. Most of these studies indicate that hypothermic treatment should be immediate or precocious (within 6 hours from the insult), while neuroprotection diminishes or disappears if the cooling is delayed beyond 6 hours
[27,38-42]. For this reason, hypothermic treatment following asphyxia should be initiated as soon as possible. The duration of treatment with hypothermia varied in such experimental studies. Significant benefits were obtained when moderate hypothermia was maintained for at least 12–24 hours, but it has been suggested that more prolonged treatment, up to 72 hours
[42], may be necessary if the interval before induction of hypothermia is prolonged
[43]. In sheep fetuses a rebound of epileptic activity has been reported after rapid heating
[43]. Finally, hypothermia appears to be more neuroprotective in animal exposed to moderate, rather than severe asphyxia
[40,44].

In conclusion, there is a strong experimental evidence that moderate hypothermia in asphyxiated animals produces behavioral and histological benefits both in the short-term
[40,45], and in the long-term
[27,46-49].

### Hypothermia as a neuroprotective treatment in human neonates

In human neonates hypothermia has been described for the first time as a treatment for resuscitation in the '60s, before modern techniques of resuscitation were introduced
[50]. In such occasions, hypothermia was used only for short periods of time after failed resuscitation, but details regarding side-effects or clinical long-term outcome of these infants were not provided
[51-55]. Since the late '90s, on the basis of the above mentioned animal studies, pilot studies with selective brain hypothermia associated with generalized mild hypothermia or generalized moderate hypothermia between 35.5 and 33.0°C for 48–72 hours, have been performed in infants with HIE demonstrating the feasibility of this treatment in term infants
[56-62]. In the early 2000, the first cases reports showed better neurodevelopmental outcomes in cooled asphyxiated infants: whole-body hypothermia was observed to reduce the damage of thalami, basal ganglia, and white matter, while selective brain hypothermia appeared to be more effective in protecting the cortex
[63-65].

So far, seven randomized controlled trials regarding the efficacy of therapeutic hypothermia for the treatment of neonatal encephalopathy have been published
[66-72]. Two such trials adopted the selective cerebral hypothermia
[66,72] and five the total-body hypothermia
[67-71]. All of these trials, powered to detect a difference in the primary composite outcome of death and/or disability, demonstrated the benefits of hypothermia. A meta-analysis of the first trials showed that moderate hypothermia reduced death or disability at 18 months with a risk ratio of 0.81 (95% CI, 0.71-0.93) and a number needed to treat (NNT) of 9
[73]. The first data from follow-up of newborns enrolled in the CoolCap Trial and NICHD Trial showed that neurodevelopmental outcomes calculated at 18–22 months of life predicted the functional outcomes into childhood
[74,75].

Overall, if the small study of Eicher is excluded
[76], major trials suggest that cooling is a safe procedure in newborns. Recent reviews concluded that bradycardia and thrombocytopenia were the only clinical, though benign, adverse effects that were more common with hypothermia
[77-79]. Therapeutic hypothermia has recently been included in the Guidelines of International Consensus on Cardiopulmonary Resuscitation and Emergency Cardiovascular Care Science and in the recommendations of the American Heart Association
[80,81].

Neuroprotective drugs may enhance the efficacy of hypothermia for the treatment of neonatal HIE
[82]. However, there are no studies that have explored the combined treatment with hypothermia and topiramate in asphyxiated newborns.

### Topiramate

Topiramate (TPM) is an anticonvulsant agent widely used in adults and children, characterized by good absorption, high bioavailability, and good tolerability
[83]. TPM has multiple mechanisms of action, including glutamate-receptors inhibition
[83,84], which implies a potential as neuroprotective agent. TPM did indeed demonstrate neuroprotective properties against hypoxic ischemic brain damage, both *in vitro* and in animal models, and was recently proposed as an innovative neuroprotective therapy for ischemic stroke
[85-92] and neonatal hypoxic-ischemic cerebral injury
[93]. In neuronal cultures, cell damage induced by oxygen-glucose deprivation
[91] or excitotoxic glutamate or kainate concentrations
[94], was consistently attenuated by TPM. In animal models of transient global cerebral ischemia intravenous, intraperitoneal, or oral TPM reduced the severity of cerebral damage either alone
[86-89] or with hypothermia
[90] in a dose-dependent manner, with neuroprotective doses ranging from 5–200 mg/kg, usually in single administration
[87-91]. TPM was also demonstrated to exert neuroprotective effects against periventricular leukomalacia
[92].

The neuroprotective mechanisms of TPM appear to be related not only to AMPA and kainate receptors inhibition
[92,94-97], but also to blockade of Na^+^ channels
[98], high voltage-activated calcium currents
[85], carbonic anhydrase isoenzymes
[99], and mitochondrial permeability transition pore (MPTP)
[100].

To date, no clinical study has been published to prove an additive or synergistic action of TPM combined with hypothermia in newborns with HIE.

We previously reported that TPM pharmacokinetic properties at the dose of 5 mg/kg appear to be modified by concomitant hypothermia
[101]. Likewise observed with other poorly metabolized drugs
[102], hypothermia reduces TPM clearance and slows absorption and elimination processes
[103].

Although long-term effects on cognitive functions of TPM administration in early life remain to be assessed, short-term safety is reassuring enough to support its evaluation in clinical trials that explore its possible additive neuroprotective action
[104]. The gap between effective and neurotoxic doses is greater for TPM than for other antiepileptic drugs
[103], and short-course therapy appears to have few neurotoxic effects. Regarding TPM long-term effects, in asphyxiated animal models treated with TPM, no cognitive deficit was demonstrated
[91], and in epileptic neonate rodents, TPM was safer than phenobarbital or benzodiazepines
[103,105]. Neuronal death occurred at doses of 50 mg/kg, which are considerably higher than doses used in common therapeutic schedules.

### Hypothesis

In conclusion, several *in vitro* and *in vivo* experimental studies have demonstrated that both, hypothermia and TPM, are able to reduce post-ischemic neuronal damage. So far no study has investigated whether the combined action of these procedures may be additive to their individual neuroprotective potential. We hypothesize that the combination treatment with moderate whole-body hypothermia associated with TPM administration is safe and enhances the neuroprotective properties of hypothermia for the treatment of neonatal HIE.

### Objectives

#### Major objectives: safety and efficacy of TPM associated with moderate whole-body hypothermia

The first purpose of this study is to confirm the safety of TPM administration in asphyxiated newborns. For this purpose, cardiac and respiratory parameters (heart frequency, blood pressure, oxygen saturation, respiratory support), will be continuously monitored. Blood samplings will be performed to check renal, liver and metabolic balance.

TPM is considered to be safe and generally well tolerated in children. The safety profile of TPM might be different in neonates with HIE treated with hypothermia than in adults receiving chronic therapy for epilepsy. TPM can cause metabolic acidosis, especially in pediatric patients, because of carbonic anhydrase inhibition at proximal renal tubule with consequent renal loss of bicarbonate
[106,107]. In as many as 48% of adults and 67% of children with epilepsy treated with TPM, a variable degree of metabolic acidosis develops. However, in most reported cases, bicarbonate levels did not decrease to be clinically significant. Only 11% of patients had serum bicarbonate levels <17 mEq/L
[106,108] and symptomatic cases were successfully treated with sodium bicarbonate supplementation
[106]. Although this observation is reassuring, metabolic acidosis is usually severe in neonates with HIE, who have metabolic acidosis because of both asphyxia and renal impairment. In infants, metabolic acidosis usually occurs after 8 to 26 days of TPM treatment, with dosages as high as 8.2 to 26 mg/kg/day
[109]. Similar to other carbonic acid anhydrase inhibitors, long-course TPM therapy is associated with increased risk of nephrolithiasis in adults
[106,107]. Angle closure glaucoma and acute myopia are additional, though potentially reversible, adverse events related to TPM treatment in the pediatric age
[106,107,110]. In a safety study, we found no signs of metabolic acidosis in newborns co-treated with moderate hypothermia and TPM; abdomen ultrasound scanning did not show kidney stones and ophthalmological evaluation was normal in all treated newborns
[104].

The second objective of this study is to evaluate the efficacy of TPM add-on therapy, evaluating the clinical outcome of enrolled newborns. The neurological and neuroradiologic outcome of newborns treated with hypothermia plus TPM will be compared to the outcome of control group that received hypothermia alone.

## Methods/Design

### Study population-setting

Term newborns delivered at gestational age higher than 36 weeks and with birth weight higher than 1800 g admitted for HIE to the Neonatal Intensive Care Units (NICUs) of A. Meyer University Children’s Hospital, Florence, of the Santa Chiara University Hospital of Pisa and of the La Sapienza University of Rome.

### Study design

Multicenter interventional pilot randomized controlled trial to compare the safety and efficacy of TPM add-on therapy associated to the conventional approach (treatment with whole-body moderate hypothermia).

#### Hypothermia

All newborns who will satisfy admission criteria will be treated with moderate (33.5°C) hypothermia for 72 hours. Outborn patients will be initially cooled to 35°C at the birth hospital, avoiding heating and using ice packs during the transfer to NICU. In all the centers a cooling blanket with an esophageal probe will be used to induce hypothermia; the esophageal temperature will be lowered by the blanket’s servomechanism. Rectal temperature will be monitored by a rectal probe connected to cardiomonitor. After 72 hours of hypothermia, all newborns will be gradually re-warmed up to 36.5-37°C over the following 6–12 hours (0.5°C/h). Vital parameters will be continuously monitored under hypothermia.

Half of these newborns will be subjected to additional treatment with oral topiramate.

#### Topiramate

TPM (Topamax, Janssen-Cilag, Cologno Monzese, Milan, Italy) will be administered by orogastric tube as enteric-coated granules mixed with water at the beginning of hypothermia for the first three days of life, for a total amount of 3 doses per patient. Newborns will receive 10 mg/kg once a day, a dosage usually used in infants
[111-113] and neonates
[114-117]. TPM plasma concentrations will be measured as previously reported
[118].

#### Monitoring

The following respiratory and hemodynamic parameters will be registered before starting hypothermia and then at hours 0, 6, 12, 18, 24, 30, 36, 42, 48, 54, 60, 66, 72 of hypothermia, and after the re-warming process: respiratory rate, oxygen saturation (SaO_2_), fractional inspired oxygen (FiO_2_), systolic, diastolic and mean arterial pressures, heart rate. The following blood tests will be performed in all newborns at hypothermia hours 0, 24, 48, 72 and after re-warming process: blood gas analysis (corrected for body temperature), serum electrolytes, liver and renal function tests, creatine-kinase, creatine-kinase MB isoenzyme, lactate dehydrogenase, troponin IC, complete cell blood count, C-reactive protein, procalcitonin and coagulation tests.

#### Clinical course and concomitant treatments

A central venous line will be placed in all patients. Fluid intake will be started at 60–70 mL/kg and increased of 10–20 mL/kg each day, basing on changes in body weight and serum electrolytes levels. Minimal enteral feeding will be allowed with human milk from the first day of life. In case of respiratory failure newborns will be put on patient triggered ventilation. Neonates who will develop seizures will be treated with phenobarbital, (loading dose 20 mg/kg, followed by 1.5-2.5 mg/kg every 12 hours). In case of resistance to phenobarbital, midazolam will be used with a dose-initial bolus of 0.15 mg/kg, followed by a continuous infusion (1 μg/kg/min) increased by 0.5-1 μg/kg/min every 2 minutes until a favourable response and up to a maximum dose of 18 μg/kg/min
[117]. In case of hypotension, defined as a mean arterial blood pressure <40 mmHg, single or multiple normal saline boluses will be administered (10–20 mL/kg), and in case of refractoriness, dopamine, dobutamine, norepinephrine or terlipressin
[119] will be progressively added. Newborns will receive analgesia with Fentanyl at a dose of 1 μg/kg/h, since hypothermia causes agitation and reducing the threshold of pain.

### Neurological follow-up

The duration of follow-up necessary for possible neuro-motor disabilities and cognitive loss will be 24 months.

Every newborn will be evaluated beyond the neonatal period, at 1, 3, 6, 12, 18 and 24 months of life. Standard EEG will be evaluated within one week and will be repeated if abnormal. Within the first week and three months of age, newborns will be studied with Neonatal Hammersmith neurological examination and General Movement (GMs) assessment
[120]. The Hammersmith Infant Neurological Examination
[121,122] will be performed between 3 and 6 months of life. The mental and motor development will be evaluated with the Bayley Scales of Infant and Toddler Development 3^rd^ edition
[123] measure at 12, 18 and 24 months. Bayley scales will be used to measure the major areas of development: cognitive, language, motor, social-emotional and adaptive functioning.

Visual function will be assessed in the first ten days of life by means of a recently published battery of behavioural tests designed to assess various aspects of visual function
[124,125], which includes items that assess ocular movements (spontaneous behaviour and in response to a target), the ability to fix and follow a black/white target (horizontally, vertically, and in an arc), the reaction to a colored target, the ability to discriminate between black and white stripes of increasing spatial frequency, and the ability to keep attention on a target that is moved slowly away from the infant. Visual function will be evaluated again at 4 ½, 6 and 12 months with particular regards to binocular visual acuity, measured by means of standardized instruments based on preferential force choice (Teller acuity cards), stereopsis and ocular motricity.

Acoustic function will be monitored until 24 months.

Neurologists responsible of clinical follow-up will be blindfolded about which newborns have been treated with TPM in addition to hypothermia.

#### Neuroradiologic follow-up

Standard cerebral magnetic resonance imaging (MRI), diffusion tensor imaging (DTI) and spectroscopy will be performed at the end of the hypothermic treatment within the first week, at three months and at 18 months.

Neuroradiologists responsible of follow-up will be blindfolded about which newborns have been treated with TPM in addition to hypothermia.

### Inclusion criteria

The treatment with therapeutic hypothermia will be reserved to newborns with gestational age ≥ 36 weeks and birth weight ≥ 1,800 g who will fulfill the following criteria:

1. Metabolic criteria: Apgar score ≤5 at 10 min, or persisting need for resuscitation, including endotracheal intubation or mask ventilation for more than 10 min after birth, or acidosis (pH ≤7.0 and/or base deficit ≥ −16 mmol/L in umbilical cord blood or arterial, venous, or capillary blood) within 60 min from birth;

2. Neurological criteria (modified from Sarnat and Sarnat
[126]): moderate to severe encephalopathy consisting of altered state of consciousness (irritability, lethargy, stupor, or coma) and ≥ 1 of the following signs: hypotonia, or abnormal reflexes including oculomotor or pupil abnormalities, or absent or weak suctioning, or clinical seizures;

3. aEEG criteria: “moderately abnormal” indicates a background tracing with upper margin >10 μV and lower margin ≤5 μV; “severely abnormal” pattern refers to a tracing with upper margin <10 μV and lower margin <5 μV; often this is accompanied by bursts of high voltage activity (“burst suppression”). Seizures are identified as periods of sudden increase in voltage, accompanied by narrowing of the band of aEEG activity followed by a brief period of suppression or by a build up of rhythmic activity of increasing amplitude and decreasing frequency
[127].

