### Experimental plan and data analysis

Based on the medical literature, the mean incidence of the combined frequency of mortality and severe neurodevelopmental disability in survivors at 18 months of age is approximately 50%. In fact this percentage is 55% in the cool Cap study
[66], 44% in the NICHD study
[68], 45% in the TOBY trial
[69], 51.4% in the ICE trial
[70], and 50.9% in the neo.nEURO.network study
[71]. We hypothesize that treatment with TPM may reduce the incidence of the combined frequency of mortality and severe neurodevelopmental disability in survivors at 18 months at 15%. In order to compare the incidence of this primary outcome between newborns receiving TPM plus hypothermia (treated) and those only receiving hypothermia (control group), the estimated sample size was calculated, considering normal distribution, an alpha error of 0.05 and a power of 80 percent. The sample size for each group is 32 participants.

The three units have an overall admission rate of approximately 10 term newborns with HIE per year. Due to the high hypothetical advantages of this treatment, we estimate 90-100% rate of consent and we predict we would recruit the 64 newborns over around 24 months period with a realistic safety margin.

Mortality, the incidence of severe neuromotor disability, cortical vision, sensorineural hearing loss, developmental delay, epilepsy will be evaluated at 18 months of life.

To evaluate TPM safety, cardiac and respiratory parameters (heart frequency, blood pressure, oxygen saturation, respiratory support), will be continuously monitored. Blood samplings will be performed to check renal, liver and metabolic balance. Kruskal-Wallis test will be used to assess possible differences between newborns treated or not with TPM. The safety will be also evaluated by means of relative risk (RR)
[132]. RR will be calculated as the ratio between the probabilities of side effects in the TPM group with respect to the control group. Values of RR lower than 1, will be associated to the efficacy of the treatment.

Finally, we will evaluate the different distribution of any brain lesions on MRI brain highlighted.The RR is calculated for each item studied. An RR <1 indicates an improvement of neurological, neurodevelopmental and neuroradiologic hypothermia due to the association-topiramate.

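### The base-deficit cut-off in the metabolic inclusion criterion carries the wrong sign, so as printed the acidosis clause excludes almost no one

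*Protocol article*

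**What the plan says.** The Inclusion criteria section sets three numbered criteria: metabolic, neurological and aEEG. Its opening sentence makes them the condition for therapeutic hypothermia, so they govern cooling as well as trial entry.

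The metabolic criterion has three limbs joined by *or*. The first two begin "Apgar score ≤5 at 10 min, or persisting need for resuscitation", the second covering intubation or mask ventilation for more than 10 min. The third is "acidosis (pH ≤7.0 and/or base deficit ≥ −16 mmol/L in umbilical cord blood or arterial, venous, or capillary blood"), within 60 min of birth. Inside that third limb, pH and base deficit are joined as "pH ≤7.0 and/or base deficit", so either alone is enough.

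The neurological criterion asks for "moderate to severe encephalopathy consisting of altered state of consciousness (irritability, lethargy, stupor, or coma") plus at least one further sign. The base-deficit threshold appears nowhere else in the article.

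**The concern.** Base deficit is a positive number when acid has accumulated, and larger values mean worse acidosis. A lower bound of −16 therefore sits far on the alkalotic side of zero. It conflicts with the word acidosis that introduces it and with the pH limit of 7.0 beside it.

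The abstract bases entry on early metabolic, clinical and EEG signs together. Of the three numbered criteria, only the metabolic one directly documents a perinatal hypoxic-ischemic insult; the other two describe the encephalopathy and not its cause. If the acidosis limb lets nearly everyone through, the metabolic criterion no longer does its part of the selection. The threshold is also meant for use at three hospitals, on infants who must be admitted within 6 hours of life, and staff should not have to correct it in their heads.

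**Working it through.** **Inputs** (all from the Inclusion criteria section)

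- Printed threshold: base deficit (BD) ≥ −16 mmol/L.
- Connector within the acidosis limb: and/or, so BD alone is sufficient.
- Connector between the metabolic limbs: or, so the acidosis limb alone is sufficient.

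The threshold is stated, not derived, so there is no calculation in the plan to reproduce. The check is one of sign and direction.

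**Step 1: sign.** BD = −BE, where BE is base excess.

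- Printed: BD ≥ −16 ⇔ −BE ≥ −16 ⇔ BE ≤ +16.
- Sign removed: BD ≥ 16 ⇔ −BE ≥ 16 ⇔ BE ≤ −16.

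**Step 2: which values pass.** The third column tests whether the line could be rescued by treating the number as a base excess with the printed inequality (BE ≥ −16).

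| BE (mmol/L) | Printed: BD ≥ −16 | Number read as BE ≥ −16 | Sign removed: BD ≥ 16 |
|---|---|---|---|
| +20 | fail | pass | fail |
| +16 | pass | pass | fail |
| +5 | pass | pass | fail |
| 0 | pass | pass | fail |
| −5 | pass | pass | fail |
| −10 | pass | pass | fail |
| −15 | pass | pass | fail |
| −16 | pass | pass | pass |
| −20 | pass | fail | pass |
| −25 | pass | fail | pass |

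As printed, only BE above +16 fails. Reading the number as base excess does not help: BE of 0 to −15 still qualifies, and the most acidotic infants (−20, −25) are turned away. Only the version without the minus sign selects acidosis.

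**Step 3: distance.** 16 − (−16) = 32 mmol/L on the base-deficit scale. Every BD from −16 up to just under 16 changes from pass to fail on correction.

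**Step 4: illustration under assumption.** The article gives no distribution of base excess. Assuming normal distributions, the share meeting each version is:

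| Assumed BE mean (SD) | Printed | Sign removed |
|---|---|---|
| −3 (3) | >99.99% | <0.01% |
| −5 (4) | >99.99% | 0.3% |
| −10 (6) | >99.99% | 15.9% |
| −15 (6) | >99.99% | 43.4% |

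The means and SDs are assumptions. Over this range the printed clause barely excludes anyone, whichever is chosen. The table describes this one clause and not trial entry.

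**Step 5: carry-through.** Because of the two connectors, an infant with BD 0, pH above 7.0, Apgar above 5 and no prolonged resuscitation meets the metabolic criterion as literally printed.

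**The case against.** The strongest reply is that this is a mix of base-deficit and base-excess notation that would mislead nobody. The parenthesis qualifies the word acidosis, an infant with normal pH and BD 0 is not acidotic, and the magnitude of 16 is clear. On that view the 32 mmol/L gap describes a reading no screener would use, and this is an erratum.

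Much of that stands. A neonatologist would probably infer the intended rule. Even on the literal reading, an infant must still show moderate to severe encephalopathy, and aEEG criteria are listed. The Study population-setting section limits the population to infants admitted for HIE, the Exclusion criteria section removes encephalopathy of other origin, and eligible infants are stratified by aEEG into moderate or severe HIE. The rule is applied before randomization and equally to both arms, so it does not bias the comparison.

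These points limit the importance of the error without making the text right. The exclusion of other encephalopathies does not supply positive evidence of asphyxia, which is what the metabolic criterion is for. Both literal readings of the number give the wrong rule, and nothing elsewhere in the article corrects it.

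**Conclusion.** The threshold is wrong as written. The printed rule is BE ≤ +16 mmol/L; the evident intention is BE ≤ −16 mmol/L, that is, BD ≥ 16 mmol/L. The cut-offs are 32 mmol/L apart, and the printed one lets the acidosis limb, and through it the metabolic criterion, pass practically any newborn with a blood gas in the first hour.

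The effect on the trial is limited. It is not open to almost everyone, the randomized comparison is not biased, and the stated sample-size calculation does not use this cut-off. How many extra infants a literal application would admit cannot be estimated: the other criteria still apply, and some infants qualify anyway through Apgar, resuscitation or pH.

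The conclusion rests on the standard definition of base deficit as minus base excess. That 16 is the intended magnitude is an inference from the context. The correction should be made because this is an operative eligibility threshold.

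**What to change.** In the Inclusion criteria section, replace the base-deficit condition with base deficit ≥ 16 mmol/L, or equivalently base excess ≤ −16 mmol/L. Make the same change in any screening form that repeats the line; no form is shown, so this needs checking. The clinical team should confirm 16 as the intended value.

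The cost is one deleted minus sign per document, with no effect on sample size, visits or analysis.
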